## Analysis Population

- Intent to treat (ITT): It is defined as all subjects who follow the ITT principle.
- Per-Protocol Set (PPS): PPS is a subset of ITT. It is defined as the subjects who have no major protocol deviations or protocol deviations that have major impact on the study results during the study.
- Safety Set (SS): It refers to the subjects who are enrolled and receive at least one dose of the investigational drug and constitute the SS for this study.
- The efficacy evaluation in this study will be based on ITT and PPS, where ITT is the primary analysis set. Safety analysis will be based on SS.

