| **Exclusion criteria** | Patients with any of the following are not to be enrolled in the study:   1. Multiple types of cancer, or accompanied by tumors other than rectal cancer 2. Having received any anti-cancer treatment (surgery, medication, etc.) within the past 5 years 3. Recent history of major surgery 4. Conditions affecting the absorption of capecitabine through the gastrointestinal tract (such as inability to swallow, nausea, vomiting, chronic diarrhea, etc.) 5. Having any type of uncontrolled, severe, accompanying disease, allergic to any component of the study; estimated survival period≤5 years due to any reason 6. Preparing or previously having undergone organ or bone marrow transplantation 7. Receiving immunosuppressive or systemic hormone therapy within 1 month before inclusion for immunosuppression 8. For patients with a history of central nervous system diseases, the investigator needs to judge whether the clinical severity hinders signing the informed consent or affects the patient's oral medication compliance 9. Other situations/problems that may affect the research results or lead to the termination of the study (such as alcohol abuse, drug abuse, etc.) 10. Pregnant or lactating women, or women planning to conceive during treatment |
| **Statistical considerations** | The primary endpoint is pathological complete response (pCR). The trial is designed as a single-arm Phase II study with 80% power to detect an increase in the pCR rate from 5% (historical control for pMMR/MSS LARC after standard long-course radiotherapy) to 20% with a one-sided alpha of 0.05. Accounting for an anticipated 10% drop-out rate, a total of 30 patients will be enrolled. |
| **Period during which study was conducted** | First patient enrolled: 2023-01-01.  Planned enrollment duration: approximately 24 months to accrue ~30 patients.  Planned follow-up after treatment: 5 years (for disease-free survival and overall survival assessments). |

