# Study Endpoints

## Primary Endpoints

Pathologic complete response rate (pCR) based on TRG scoring criteria: refers to the percentage of subjects with no viable tumor cells (including lymph nodes, stage ypT0N0M0) seen under light microscopy.

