## Subject withdrawal of study treatment

Subjects can withdraw from the trial at any time on their own, or are withdrawn by the investigator due to safety or behavioral reasons, or because they are unable to comply with protocol-required study visit times or procedures at their site.

Reasons for withdrawal of a subject from the study may include:

1. Patients for whom combined organ resection is necessary during the operation;
2. Patients with distant metastasis confirmed during the operation, including liver, pelvic cavity, ovaries, peritoneum, and distant lymph node metastasis;
3. Patients who require emergency surgical resection due to intestinal obstruction, intestinal perforation, intestinal bleeding, etc;
4. Patients who request to withdraw from the study cohort for various reasons after being included in the study;
5. Patients with other non-tumor conditions that prevent them from continuing to receive this treatment plan;
6. Patients who cannot complete the study plan for various reasons after being included in the study;

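### The protocol withdraws patients from the study for findings made after treatment, and its circular ITT definition does not say they stay in the pCR denominator

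*Protocol*

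**What the plan says.** Section 9.2 (Analysis Population) bases efficacy on ITT and PPS, "where ITT is the primary analysis set". Its definition reads in full: "Intent to treat (ITT): It is defined as all subjects who follow the ITT principle". The Safety Set in the same section does have a working definition: enrolled and given at least one dose of the investigational drug.

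The section headed Subject withdrawal of study treatment opens its list with "Reasons for withdrawal of a subject from the study may include", so the heading concerns treatment and the text concerns the study. The six reasons include "Patients for whom combined organ resection is necessary during the operation", "Patients with distant metastasis confirmed during the operation, including liver, pelvic cavity, ovaries, peritoneum, and distant lymph node metastasis", emergency resection, and "Patients who cannot complete the study plan for various reasons after being included in the study".

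Under Primary Endpoints, pCR "refers to the percentage of subjects with no viable tumor cells (including lymph nodes, stage ypT0N0M0) seen under light microscopy". The denominator is not qualified as enrolled, treated or resected.

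On size, the Summary states: "Accounting for an anticipated 10% drop-out rate, a total of 30 patients will be enrolled". Section 9.1 gives 46 from the same rates, alpha, power and drop-out allowance.

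**The concern.** In a single-arm trial the pCR denominator is the main safeguard on the efficacy estimate, because no control arm is affected in the same way. Here some reasons for leaving the study are themselves results of the treatment strategy. A patient with metastasis found at operation cannot be ypT0N0M0. A patient without a resection specimen cannot be shown to have pCR. If such patients leave the denominator, the rate rises without any additional response.

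The primary set should prevent this, but its definition refers back to itself and no other section settles the matter. The estimate and the only hypothesis test are both exposed.

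**Working it through.** **Inputs.** From the Summary and section 9.1: null pCR rate 5%, alternative 20%, one-sided alpha 0.05, power 80%, drop-out 10%, enrolment 30 (Summary) or 46 (section 9.1). The protocol states no critical value and names no test. The success rule below is derived: exact binomial p = P(X ≥ x | n, 0.05), with success if p ≤ 0.05.

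**Reproducing the Summary's 30.** The smallest n meeting both conditions is 27, with success at 4 or more pCR: P(X ≥ 4 | 27, 0.05) = 0.0437 and P(X ≥ 4 | 27, 0.20) = 0.818. Then 27 / 0.9 = 30. The figure therefore fits a test on 27 patients after drop-outs have left. The 46 does not reproduce at 80% power. The conflict between 30 and 46 is a separate point, so both sizes are carried through.

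**Can removing non-responders change the result?**

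| Enrolled | pCR | Removed | Denominator | Rate | Exact p | Result |
|---|---|---|---|---|---|---|
| 30 | 4 | 0 | 30 | 13.3% | 0.0608 | fails |
| 30 | 4 | 1 | 29 | 13.8% | 0.0548 | fails |
| 30 | 4 | 2 | 28 | 14.3% | 0.0491 | succeeds |
| 30 | 4 | 3 | 27 | 14.8% | 0.0437 | succeeds |
| 46 | 5 | 0 | 46 | 10.9% | 0.0786 | fails |
| 46 | 5 | 5 | 41 | 12.2% | 0.0525 | fails |
| 46 | 5 | 6 | 40 | 12.5% | 0.0480 | succeeds |

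At 30, two removals suffice, fewer than the three allowed for (10% of 30). At 46, six are needed (6/46 = 13%), more than the 10% allowance.

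**Bias in the estimate.** If a share q leaves and all are non-pCR, a rate p among all enrolled becomes p / (1 − q). At q = 10%, 5% becomes 5.6% and 20% becomes 22.2%, whatever the sample size.

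**Type I error.** Assume each enrolled patient has pCR with probability 5%, leaves as a non-pCR with probability q, and otherwise stays as a non-pCR. With r leaving, the denominator is N − r and c(N − r) is its critical value. The error is the sum over r of Bin(r; N, q) × P(X ≥ c(N − r) | N − r, 0.05 / (1 − q)).

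| q (assumed) | N = 30 | N = 46 |
|---|---|---|
| 0% | 1.6% | 2.6% |
| 5% | 3.4% | 2.7% |
| 10% | 5.1% | 4.0% |
| 15% | 5.8% | 6.0% |
| 20% | 6.0% | 7.3% |

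If exactly three of 30, or six of 46, non-responders left in every trial, the error would be P(X ≥ 4 | 30, 0.05) = 6.1% or P(X ≥ 5 | 46, 0.05) = 7.9%. Those are upper figures for losses of that size, not expected values.

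**Power with everyone kept in.** The 18% column applies the 20% rate only to the 90% who remain (0.9 × 20%).

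| N | Success at | Alpha | Power at 20% | Power at 18% |
|---|---|---|---|---|
| 30 | ≥ 5 | 1.6% | 74.5% | 64.9% |
| 46 | ≥ 6 | 2.6% | 92.0% | 85.9% |

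**The case against.** The best defence is that withdrawal is not exclusion from analysis. ITT conventionally keeps everyone enrolled, ITT is the primary set, the endpoint speaks of subjects rather than resected subjects, the list gives what reasons may include, and a SAP could settle the counting. Much of this stands: no sentence orders these patients out of the denominator. But the conventional meaning conflicts with a sample size of 30 that reproduces only if drop-outs leave. The protocol also chose to define its analysis sets, so a circular primary definition is an error in this document and not detail left for later.

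Four stronger readings are tempting and are not supported.

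- A reader might infer that nearly all the listed reasons imply non-pCR. Only metastasis found at operation does so by definition, through the M0 in Primary Endpoints; Efficacy Evaluation words pCR on the primary tumour alone. Combined organ resection proves neither residual tumour nor incurability, and patient request, non-tumour conditions and inability to complete the plan say nothing about pathology.
- A reader might take the ITT sentence to mean those who complied. That conflicts with the PPS, a subset of ITT formed by removing major deviators.
- A reader might infer that alpha is broken in general. With random loss at the planned 10%, all non-pCR, it is barely exceeded at 30 and held at 46. If loss were unrelated to response, the same sum with 5% in place of 0.05 / (1 − q) gives about 3.6% and 2.6%.
- A reader might treat 27 evaluable and success at 4 pCR as the plan's own rule. Both are inferred from its rates and alpha.

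**Conclusion.** The point holds as a defect of definition with a real route to bias. The protocol withdraws patients from the study for findings made after treatment, does not say who belongs to its primary set, and has a Summary sample size that fits drop-outs leaving the denominator. Any non-responder dropped raises the pCR rate at either sample size.

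The effect on the test is moderate and depends on the enrolment figure. At 30, two withdrawn non-responders can turn 4 pCR into a success. At 46, the same change for 5 pCR needs a loss above the planned 10%. Under random loss with all leavers non-pCR, type I error goes above 5% only slightly at 30 with 10% loss, and reaches 6.0% (30) and 7.3% (46) at 20% loss. These figures rest on the derived exact rule and on the assumed share and response status of those who leave.

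**What to change.** In section 9.2, define ITT explicitly as all enrolled patients, or all who started study chemoradiotherapy, and use one definition throughout. State that in the primary analysis any patient without a specimen meeting the ypT0N0M0 definition, for any reason, counts as non-pCR. Keep the rate among resected patients as supportive.

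In the withdrawal section, reconcile the heading (treatment) with the text (study), and state that the listed reasons do not remove a patient from the ITT denominator or from follow-up. This concerns counting only and leaves clinical decisions as they are.

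In section 9.1 and the Summary, state the success rule and restate the power for the full denominator, using the figures above, once the enrolment number is settled.

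The text changes are short. The cost is a slightly lower reported pCR rate and, at 30, a stated power below 80% (74.5%, or 64.9% if the 20% rate applies only to those who remain), so the sample size has to be looked at again. At 46 the power stays above 80% in both cases.

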## Secondary Endpoints

- Sphincter preserving rate：proportion of patients with preserved anal sphincter

Time Frame: instantly after surgery;

- Immune-related adverse event rate: adverse event rate that is deemed to be associated with PD-1 inhibition

Time Frame: from commencing of PD-1 inhibition to the 30th day after surgery;

- Treatment-related adverse event rate: adverse event rate that is deemed to be associated with all treatments

Time Frame: from commencing of treatment to the 30th day after surgery;

- Incidence rate of surgical complications: incidence rate of surgical complications within 30 days after surgery

Time Frame: within 30 days after surgery;

Exploratory Endpoints

- Longitudinal single-cell RNA-seq (scRNA-seq) and single-cell TCR-seq (scTCR-seq) of tumor tissue and matched peripheral blood to identify immune programs of response vs resistance

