# Study medication

## Overview of investigational product

In the study, study drugs are defined as Sintilimab.

|  | Sintilimab |
| --- | --- |
| Manufacturer | Innovent, China |
| Dose Form | Injection fluid |
| Strength | 100 mg |
| Route of Administration | Intravenous |

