### Criteria for judging the relationship between adverse event and study drug

The collection of adverse events begins from the time of informed consent and continues through the end of the safety follow-up period. All adverse events must be collected and reported in the form of clinical report, regardless of the relationship between the event and investigational drug and whether the drug is used or not. Any discomfort or abnormal changes in objective laboratory test indicators complained of during treatment should be recorded truthfully, and the severity, duration, treatment measures and outcome of adverse events should be indicated. The investigator should comprehensively determine the relationship between adverse events and the investigational drug, such as whether the occurrence of adverse events has a reasonable time sequence with the medication, the characteristics of the investigational drug, the toxicological and pharmacological effects of the investigational drug, whether the subject uses other concomitant drugs, the subject's underlying diseases, medical history, family history, and challenge and rechallenge reactions. The possible association between adverse events and investigational drug is evaluated according to the five-level classification of "definitely related, possibly related, possibly unrelated, definitely unrelated and indeterminable".

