The **causal relationship** to study drug is determined by a physician and should be used to assess all adverse events (AE). The casual relationship can be one of the following:

**Related**: There is a reasonable causal relationship between study drug administration and the AE.

**Not related**: There is not a reasonable causal relationship between study drug administration and the AE.

The term "reasonable causal relationship" means there is evidence to suggest a causal relationship.

An appropriate SAE form (e.g. ex-US = CIOMS form or USA = Medwatch form) should be used to report SAEs to BMS. If the Sponsor-Investigator prefers to a study specific/Institutional form, it must be sent to the BMS ISR Trial Manager prior to study initiation for internal BMS review to ensure that at a minimum all of the data elements on the CIOMS form are present.

Please include the BMS Protocol number on the SAE form or on the cover sheet with the SAE form transmission.

- - The CIOMS form is available at: <https://cioms.ch/cioms-i-form/>
  - The MedWatch form is available at: https://www.fda.gov/safety/medical-product-safety-information/medwatch-forms-fda-safety-reporting

**NOTE**: If a CIOMS I or Medwatch form is selected for reporting, the investigator causal assessment must be provided in the narrative section, otherwise the BMS form must be used.**NOTE**: For studies with long-term follow-up period in which safety data are being reported, include the definition of end date of SAE collection.

SERIOUS ADVERSE EVENT COLLECTION AND REPORTING

All Serious Adverse Events (SAEs) that occur following the subject’s written consent to participate in the study through *100* days of discontinuation of dosing must be reported to BMS Worldwide Safety, whether related or not related to study drug**. If applicable,** SAEs must be collected that relate to any follow-up protocol-specified procedure (eg, a follow-up skin biopsy).

- Following the subject’s written consent to participate in the study, all SAEs, whether related or not related to study drug, are collected, including those thought to be associated with protocol-specified procedures. The Investigator should report any SAE occurring after these aforementioned time periods, which is believed to be related to study drug or protocol-specified procedure.
- An SAE report should be completed for any event where doubt exists regarding its seriousness;

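### The Safety Set admits only sintilimab recipients, but the treatment-related AE rate covers all treatments from the start of chemoradiotherapy

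*Protocol*

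**What the plan says.** **Analysis set.** Section 9.2 (Analysis Population) restricts the Safety Set to "subjects who are enrolled and receive at least one dose of the investigational drug" and adds, with no exception, "Safety analysis will be based on SS". The section Overview of investigational product fixes what that drug is: "In the study, study drugs are defined as Sintilimab".

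**Endpoint.** Secondary Endpoints defines the treatment-related AE rate as the "adverse event rate that is deemed to be associated with all treatments", over a window running "from commencing of treatment to the 30th day after surgery". No severity threshold is set.

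**Order of treatment.** Under Treatment Regimen, the Protocol Summary gives 5 weeks of chemoradiotherapy first, with sintilimab from the 15th day after it ends. Dosing Regimen likewise places sintilimab after radiotherapy.

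**Causality.** Under the criteria for judging the relationship of an AE to study drug, "The possible association between adverse events and investigational drug is evaluated according to the five-level classification". Section 7.2.4 (Reporting system of serious adverse events) gives a second, two-level scale for all AEs, on which an event is related if "There is a reasonable causal relationship between study drug administration and the AE".

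**The concern.** The endpoint starts with the first treatment, but its analysis set opens only to patients who reach the last treatment before surgery. Someone who begins chemoradiotherapy and leaves before sintilimab has been exposed to a treatment that the endpoint covers, yet counts in neither numerator nor denominator.

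The causality scales have a related gap. An endpoint spanning all treatments needs a judgement of relatedness to each of them, and both written scales name only the drug.

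At stake is one descriptive secondary rate. But this is a single-arm trial of a few dozen patients, safety is one of its main outputs, and no control arm exists in which the same exclusion would operate.

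**Working it through.** The protocol states no figure for this point, so there is none to reproduce. The check compares definitions first and then illustrates the size.

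**Step 1: who is excluded.**

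| Element | Treatment-related AE rate (Secondary Endpoints) | Safety Set (9.2) |
|---|---|---|
| Treatments covered | all | sintilimab only |
| Entry | start of chemoradiotherapy | first sintilimab dose |
| Approximate day of entry | 1 | 5 × 7 + 15 = 50 |

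The gap is about 7 weeks. Exits in that interval are foreseen: the section on subject withdrawal lists emergency surgery, patient request, non-tumour conditions that prevent continuation, and inability to complete the plan. The sample-size text anticipates 10% drop-out without saying when it occurs.

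**Step 2: formula.** Let N patients start treatment and k of them stop before sintilimab. Let p be the related-AE rate among the N − k who receive sintilimab, and q the rate among the k who do not.

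- Rate in the Safety Set as written: p
- Rate in all treated patients: [p(N − k) + qk] / N
- Difference, all treated minus Safety Set: (k/N)(q − p)

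The sign therefore depends on whether early stoppers have more or fewer related AEs than the others.

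**Step 3: illustration.** Assumptions: every early stopper has a related AE (q = 1), and p is about 20% or 50%, rounded to whole patients. None of k, p or q is in the documents. N is 30 in the Protocol Summary and 46 in section 9.1; that conflict is a separate matter, so both are shown.

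| N | k | Safety Set as written | All treated | Difference (points) |
|---|---|---|---|---|
| 30 | 1 | 6/29 = 20.7% | 7/30 = 23.3% | 2.6 |
| 30 | 1 | 14/29 = 48.3% | 15/30 = 50.0% | 1.7 |
| 30 | 3 | 5/27 = 18.5% | 8/30 = 26.7% | 8.1 |
| 30 | 3 | 14/27 = 51.9% | 17/30 = 56.7% | 4.8 |
| 46 | 3 | 9/43 = 20.9% | 12/46 = 26.1% | 5.2 |
| 46 | 3 | 22/43 = 51.2% | 25/46 = 54.3% | 3.2 |
| 46 | 5 | 8/41 = 19.5% | 13/46 = 28.3% | 8.7 |
| 46 | 5 | 20/41 = 48.8% | 25/46 = 54.3% | 5.6 |

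For scale, 10% of 30 is 3 and 10% of 46 is 4.6, so k = 3 and k = 5 put essentially all the anticipated drop-out before sintilimab. They mark the upper end.

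**Step 4: where the effect shrinks or reverses.**

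- High any-grade rate: with N = 30, k = 3 and 24 of 27 affected, 24/27 = 88.9% becomes 27/30 = 90.0%, a difference of 1.1 points. If all are affected, both rates are 100%.
- Early stoppers without related AEs (q = 0): with N = 30 and k = 3, 14/27 = 51.9% becomes 14/30 = 46.7%, so the Safety Set rate is 5.2 points too high.

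**Step 5: causality.** Neither written scale has a rating for radiotherapy, chemotherapy or surgery. The nearest provision, in 7.2.4, concerns SAEs thought unrelated to study drug but possibly linked to the conditions of the study. It asks for that link in the report narrative, so it covers SAEs only and in free text.

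**The case against.** The strongest reply is that little information is lost. AEs are collected from consent onward, and the protocol says so even for patients who never use the drug (Definition of Adverse Events, and the section on the relationship to study drug). SAEs are reported from consent. A chemoradiotherapy death would be captured and reported. The endpoint itself calls for a judgement against all treatments, Dose Adjustments requires reasons for interruptions to be recorded, and the case report form is not shown. All of this stands. A reader might infer that early toxicity goes unrecorded, or that relatedness to the other treatments is never noted; the documents do not support either. What none of these passages does is return the excluded patients to the analysis set or supply a rating scale for the other treatments.

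A reader might also infer that the rate is certain to be biased low. That does not follow. The listed withdrawal reasons include several unconnected with toxicity, and Step 4 shows that the direction can reverse. An example restricted to severe events would overstate the evidence too, because the endpoint has no grade limit.

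Two further points limit the finding. The sintilimab-based set suits the immune-related AE rate, whose window opens with PD-1 inhibition. And although two causality scales stand side by side, how the five levels map to related or not related can be left to the SAP; treating indeterminable events as related would be a convention, not the correction of an error.

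The reply that analysis sets belong in the SAP does not answer the core point. The protocol has already fixed this one, and an SAP that follows it inherits the mismatch.

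**Conclusion.** The population mismatch is established on the protocol's wording: section 9.2 excludes patients whom the treatment-related AE rate is defined to cover, and no other section repairs this. It affects how those patients are analysed, not whether their events are collected.

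The size is an assumption. For 1 to 3 early stops among 30, with a related AE in each and in 20% to 50% of the rest, the reported rate is about 2 to 8 points too low. It is nearly unaffected if the any-grade rate approaches 100%, and too high if early stoppers have fewer related AEs than the others. The mismatch exists in every case.

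The causality gap holds in a limited form: relatedness to chemoradiotherapy and surgery is not systematically rated, apart from SAE narratives. The primary pCR analysis is untouched.

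**What to change.** - Define the Safety Set as all enrolled patients who receive any protocol treatment (at least one radiotherapy fraction, or one dose of chemotherapy or sintilimab), and use it for the treatment-related AE rate.
- Use the sintilimab-treated subset for the immune-related AE rate and the operated subset for surgical complications.
- Rate causality separately for chemoradiotherapy, sintilimab and surgery, on a single scale. Make this change in the protocol and the case report form, since a rating not made at the time is hard to restore at analysis.

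The cost is a few lines of wording and minor additions to the case report form. Treatment, visits and sample size do not change. The reported AE rate may look less favourable.

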# Statistical analysis of data

## Sample Size

- The primary endpoint is pCR. This study has 80% power to detect an increase in pCR rate from 5% to 20% with a one-sided alpha of 0.05. Considering a 10% drop-out rate, 46 patients will be enrolled.

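### If 30 patients are enrolled and all are analysed by ITT against 5%, no pCR cut-off meets both the stated alpha and the stated power; the conflict between 30 and 46 must be settled first

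*Protocol*

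**What the plan says.** Section 9.1 (Sample Size) states: "This study has 80% power to detect an increase in pCR rate from 5% to 20% with a one-sided alpha of 0.05". It continues: "Considering a 10% drop-out rate, 46 patients will be enrolled". The Overall Design section also gives 46, in a sentence that describes a gastric cancer population.

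The Statistical considerations row of the Protocol Summary uses the same design inputs, an "increase in the pCR rate from 5% (historical control for pMMR/MSS LARC after standard long-course radiotherapy) to 20% with a one-sided alpha of 0.05", with the same 80% power, but ends differently: "Accounting for an anticipated 10% drop-out rate, a total of 30 patients will be enrolled". The summary row on the study period agrees with the smaller figure: "approximately 24 months to accrue ~30 patients".

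On the analysis, section 9.2 (Analysis Population) states: "The efficacy evaluation in this study will be based on ITT and PPS, where ITT is the primary analysis set". It defines the ITT set only by reference to the ITT principle, and does not say how a patient without a pCR assessment is counted. pCR is read on the surgical specimen (Primary Endpoints; Pathological efficacy evaluation). The sample-size text names no test and no cut-off. That may be left to a statistical analysis plan and is not the point here.

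**The concern.** An enrolment target that is inflated for drop-out normally carries the power of the smaller, evaluable group. An ITT analysis keeps the drop-outs in the denominator. If the 80% was worked out on evaluable patients, it does not automatically belong to the analysis that the protocol calls primary.

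In a trial this small the binomial steps are coarse. Moving from 27 to 30 patients in the denominator changes which cut-off respects the 5% limit. At stake are whether 4 pCRs among 30 patients would be a success, and whether the power quoted to the ethics committee and to readers is that of the primary analysis.

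**Working it through.** **Inputs.** Null rate 5%, alternative 20%, one-sided alpha 0.05, power 80%, drop-out 10% (Protocol Summary and section 9.1). N is 30 (Protocol Summary) or 46 (section 9.1 and Overall Design). The primary set is ITT (section 9.2).

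**Formula.** For a rule of success at r or more pCRs among n patients, P(X ≥ r | n, p) = Σ C(n,k) p^k (1−p)^(n−k), summed from k = r to n. At p = 5% this is alpha; at the alternative it is power.

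**Step 1: reproduce the stated sizes.** The smallest n with exact alpha ≤ 0.05 and power ≥ 0.80 is 27, with r = 4: alpha 0.0437, power 0.8177. Inflating, 27 / 0.9 = 30, which is the summary's figure. Other one-sided formulas, after inflation, give 25 (normal, null and alternative variances), 32 (continuity-corrected), 32 (arcsine), 49 (alternative variance only) and 16 (null variance only). Two-sided versions give 29, 37, 39, 63 and 19; the exact test at one-sided 0.025 gives 37. None gives 46.

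**Step 2: all 30 in the denominator, against 5%.** The probabilities of 0, 1, 2 and 3 pCRs are 0.21464, 0.33890, 0.25864 and 0.12705, which sum to 0.93923. So P(X ≥ 4) = 1 − 0.93923 = 0.0608.

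| N | Rule | Alpha at 5% | Power at 20% | Power at 18% |
|---|---|---|---|---|
| 27 | ≥4 | 0.0437 | 0.818 | 0.742 |
| 30 | ≥4 | 0.0608 | 0.877 | 0.814 |
| 30 | ≥5 | 0.0156 | 0.745 | 0.649 |
| 46 | ≥6 | 0.0263 | 0.920 | 0.859 |

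At N = 30, a cut-off of 4 or fewer breaks the alpha limit and a cut-off of 5 or more falls short of 80% power. A normal-approximation test does not avoid this. Its boundary is 30 × (0.05 + 1.645 × √(0.05 × 0.95 / 30)) = 3.46 patients, so it rejects at 4, where the true alpha is 0.061.

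**Step 3: drop-outs counted as non-pCR.** If 20% applies to the 90% who are evaluable, the ITT rate is 0.9 × 20% = 18%.

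- 5% kept as a fixed ITT benchmark: the rule ≥5 of 30 has power 0.649 (0.652 if exactly 3 of the 30 drop out).
- Null diluted in the same way, 0.9 × 5% = 4.5%: the rule ≥4 of 30 has alpha 0.0442 and power 0.814, so both targets are met.

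**Step 4: N = 46.** The rule ≥6 meets both targets at 20% and at 18% (table).

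**Step 5: sizes that work against a fixed 5%.** If the ITT rate is 20%, these are 27 or 28 (≥4), then 33 and above (at 33, ≥5: alpha 0.023, power 0.818). If the ITT rate is 18%, the smallest is 36 (≥5: alpha 0.032, power 0.801).

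**The case against.** The strongest reply is that N = 30 is not settled. Section 9.1, immediately before the analysis sets are defined, gives 46, and at 46 both targets are met with room to spare. This stands, and it makes the point conditional. It does not remove it: 30 appears twice in the summary, is the only stated size that the stated inputs reproduce, and one of the two mentions of 46 sits in text about a different cancer.

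A reader might infer that the trial's true power is simply 74%, or 65%. The documents do not support that. The 74.5% needs N = 30, all 30 in the denominator and a 20% rate in that whole group. The 65% needs two further assumptions that the protocol does not state: that unassessed patients count as non-pCR, and that 5% is a fixed benchmark for the ITT rate. The protocol does not give the denominator of its historical 5%. If the null is diluted too, at least 4 of 30 meets both targets.

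A reader might also infer that the team will carry a rule of 4 pCRs from 27 patients into the 30-patient ITT set and so exceed alpha. No such rule and no 27-patient calculation appear in the protocol. The 27 is a reconstruction that fits exactly, not a documented step, and a cut-off may stand in an analysis plan that is not shown.

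Finally, the shortfall is modest and due to discreteness: 5.5 points of power (80 − 74.5), or alpha 0.061 instead of 0.05. That is fair. The summary's calculation is sound for about 27 evaluable patients.

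**Conclusion.** The point holds conditionally. The two enrolment figures from identical inputs are the prior defect. If N is 30 and all 30 are tested against 5%, the ITT analysis cannot deliver 80% power within one-sided alpha 0.05: the best rule within the limit, at least 5 pCRs, has alpha 0.016 and power 74.5% at 20%. The mismatch is that a size matching an evaluable-patient design is paired with an ITT primary set.

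Beyond that, the result depends on how drop-outs and the benchmark are treated: about 65% with drop-outs as non-pCR and 5% fixed, or 81% at alpha 0.044 with the null diluted to 4.5%. If N is 46, power is 92% (86% at 18%) and nothing needs correcting on this point beyond stating the rule. It should be resolved before the primary analysis, but it does not invalidate the design.

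**What to change.** 1. Settle one N and use it in the Protocol Summary, Overall Design and section 9.1.
2. State the exact one-sided binomial test, the cut-off on the ITT denominator, and that patients without a pCR assessment count as non-pCR. State whether 5% is a fixed benchmark for the ITT rate.
3. Restate alpha and power for that rule. For N = 30 against a fixed 5%: success if at least 5 of 30 have pCR, alpha 0.016, power about 74% at 20%, and about 65% with 10% non-evaluable. For N = 46: at least 6 of 46, alpha 0.026, power 92%, or 86% with 10% non-evaluable.

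This costs a few sentences and no extra patients. The only downside, if N is 30, is a less favourable stated power. If the team wants 80% against a fixed 5% after counting 10% as non-pCR, the smallest size is 36, six more than 30.
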